**AIM OF THE STUDY**

The study is aiming to prove the efficacy of intravenous treatment of clarithromycin in the reduction of 28-day mortality among patients with sepsis and respiratory dysfunction. Secondary aims are the effect on overall 90-day mortality, sepsis resolution and recurrence, 28-day mortality in the subgroup of patients with septic shock and impact on genomic, transcriptomic, metabolomic, microbiome and cell population profile, especially biomarkers of sepsis-induced immunosuppression. Finally, this study aims to perform a cost-effectiveness analysis of clarithromycin compared to placebo at 90 days.

**STUDY DESIGN**

***Type of study and study sites***

This is a double- blind, randomized, placebo-controlled clinical study that will be conducted in patients admitted in the following departments of Intensive Care Medicine (ICU) and Internal Medicine in Greece and Belgium (see Appendix I):

4^th^ Department of Internal Medicine, ATTIKON University Hospital, Athens, Greece

2^nd^ Department of Critical Care Medicine, ATTIKON University Hospital, Athens, Greece

Intensive Care Unit, THEAGENEION General Hospital, Thessaloniki, Greece

Intensive Care Unit, G. GENNIMATAS General Hospital, Thessaloniki, Greece

Intensive Care Unit, Ο AGHIOS DIMITRIOS General Hospital, Thessaloniki, Greece

Intensive Care Unit, HIPPOKRATION General Hospital, Thessaloniki, Greece

Intensive Care Unit, KORGIALENEIO BENAKEIO General Hospital, Athens, Greece

Intensive Care Unit, LAIKO General Hospital, Athens, Greece

2^nd^ Department of Internal Medicine, SISMANOGLEION General Hospital, Athens, Greece

Department of Intensive Care, ERASME University Hospital, Brussels, Belgium

Department of Intensive Care, Horta Site, BRUGMANN Hospital, Brussels, Belgium

Department of Intensive Care, Brien Site, BRUGMANN Hospital, Brussels, Belgium

Department of Intensive Care, SAINT-PIERRE Hospital, Brussels, Belgium

This is a phase IV RCT and the study drug will be provided by the Sponsor. The study protocol will be submitted for approval to the Institutional Review Board and subsequently to the Regulatory Authorities of each country; these are the National Ethics Committee and the National Organization of Medicine of Greece or the Federal Agency of Drugs and Medicinal Products of Belgium. After study approval and before enrolment of the first patient, the study will be registered at the website [www.clinicaltrials.gov](http://www.clinicaltrials.gov). Patients will be enrolled after written informed consent provided by themselves or by legal representatives (first-degree relatives) in case of patients unable to consent.

***Inclusion criteria***

ALL following criteria should be met for the inclusion of a patient in the study:

- Adult patients (≥18 years)
- Patients of both genders
- Informed consent form signed by patient or by first-degree relative in case of patient unable to consent
- Negative (blood or urinary) pregnancy test for female patients of reproductive age
- Willingness to receive contraception during and seven days after the administration of the study drug.
- Presence of one or more of the following infections: hospital-acquired pneumonia (HAP), health-care associated pneumonia (HCAP), ventilator-associated pneumonia (VAP), primary Gram-negative bacteremia or intra-abdominal infections. Definitions for these infections are given below.
- Presence of sepsis as defined by the Sepsis-3 classification criteria^3^ (see definitions section below)
- Respiratory dysfunction defined as one PaO_2_/FiO_2_ ratio inferior to 200, independently of the PEEP level.
- Total SOFA points for organ dysfunctions other than the respiratory function more than 3

***Exclusion criteria***

Patients who meet ANY of the exclusion criteria below cannot be enrolled in the study:

- Denial for informed consent
- Age inferior to 18 years
- Pregnancy (confirmed by blood or urinary pregnancy test) or lactation for female patients of reproductive age.
- Unwillingness to receive contraception during and seven days after the administration of the study drug.
- HIV infection (with known CD4 cell count ≤ 200/mm^3^)
- Solid organ, or bone marrow transplantation
- Corticosteroid oral or intravenous intake greater than 0.4 mg/kg of equivalent prednisone daily over the last 15 days; anti-cytokine biological agents (e.g. anti-TNFα), anti-lymphocyte immunoglobulins, Mycofenolate Mofetil, Tacrolimus (FK506) and m-TOR inhibitors (any dose of the above within the past 3 months); Chemotherapy within the past 3 months, Leflunomide intake within the past 2 year, Rituximab within the last year; Methotrexate, Azathioprine, Cyclosporine, Cyclophosphamide (any dose of the above within the last 3 months). Splenectomy, known primary immunodeficiencies. Hydroxyurea, anti-Vascular Endothelial Growth Factor (VEGF), anti-Epithelial Growth Factor Receptor (EGFR), anti-Growth Factor Her-2 and Interferon a, b and γ intake are not considered as exclusion criteria.
- Known active neoplasms or other medical conditions unrelated to sepsis (any of the two), that are compromising short-term survival (1 month)
- Neutropenia <1000/mm^3^
- Known allergy to macrolides
- Previous participation in the study
- Administration of a macrolide for the current infectious episode

***Definitions***

Sepsis is defined by the following criteria, based on sepsis-3 classification^3^:

- Total SOFA score of 2 or more points for patients who are admitted with infection at the emergency department (see APPENDIX II) or
- Increase of admission SOFA score by 2 or more points consequent to infection, for patients already hospitalized (see APPENDIX II)

Hospital-acquired pneumonia (HAP) is defined by the presence of a new or progressive radiographic lung infiltrate in a non-intubated patient hospitalized for more than 48 hours who presents with at least two of the following clinical features:

- Core temperature equal or greater than 38°C
- Total white blood cell count more than 12,000/mm^3^
- Rales or bronchial breath sounds on physical examination
- Purulent sputum
- More than 20 breaths/minute
- Serum procalcitonin more than 0.25 ng/ml
- Gram stain of tracheobronchial secretions or bronchoalveolar lavage fluid indicating the predominance of Gram-negative bacilli

Health-care associated pneumonia (HCAP) is defined by the presence of a new or progressive radiographic lung infiltrate in a non-intubated patient who has at least one of the following risk factors for HCAP^15^:

- Hospitalization the last 90 days
- Residency in a long-term care facility
- Under regular hemodialysis

AND who presents with at least two of the following clinical features:

- Core temperature equal or greater than 38°C
- Total white blood cell count more than 12,000/mm^3^
- Rales or bronchial breath sounds on physical examination
- Purulent sputum
- More than 20 breaths/minute
- Serum procalcitonin more than 0.25 ng/ml
- Gram stain of tracheobronchial secretions or bronchoalveolar lavage fluid indicating the predominance of Gram-negative bacilli^15^

Ventilator-associated pneumonia (VAP) is defined by the presence of a new or progressive radiographic lung infiltrate in a patient who is under mechanical ventilation for at least 48 hours AND who presents with at least two of the following clinical features:

- Core temperature equal or greater than 38°C
- Total white blood cell count more than 12,000/mm^3^
- Purulent tracheobronchial secretions
- Serum procalcitonin more than 0.25 ng/ml
- Gram stain of tracheobronchial secretions or bronchoalveolar lavage fluid indicating the predominance of Gram-negative bacilli^15^

Primary Gram-negative bacteremia (BSI) is defined as the isolation of at least one Gram-negative microorganism from a blood culture of a peripheral vein of a patient that is not related to infection of a central line and who presents with ALL the following features^16^:

- Core temperature equal or greater than 38°C or total white blood cell count more than 12,000/mm^3^
- Thorough clinical and radiological investigation has failed to identify the primary infection site

Intra-abdominal infection (IAI) is defined as the presence of ALL the following features^16^:

- Core temperature equal or greater than 38°C or total white blood cell count more than 12,000/mm^3^
- Radiological findings from abdominal ultrasound or abdominal computed tomography or magnetic resonance imaging consistent with one IAI or peri-operative confirmation of an IAI.

***Study drug preparation and administration***

A separate allocation sequence will be generated for each study site, following a 1:1 design. An allocation sequence will be generated as sealed envelope from a statistician with 1:1 randomization per study site. The envelope is unsealed by an unblinded investigator (or the pharmacist), who is preparing the study drug (placebo or active drug). The preparations will be visually similar and allow blinded administration. Clarithromycin is provided in a form of vial with 500mg of amorphous powder. Two vials are dissolved in 10ml of water for injection each. The prepared 20ml solution is then further diluted to a final volume of 250 ml dextrose in water 5% that is directly connected to the infusion device that leading to a catheter already inserted in a central or peripheral vein. Placebo will consist in 20 ml of water for injection, diluted to a final volume of 250 ml dextrose in water 5% that is directly connected to the infusion device leading to a catheter already inserted in a central or peripheral vein. According to the generated allocation sequence, patients of each study site can be randomly assigned to one of the following two groups:

- *Placebo*; patients receive water for injection at a volume of 20ml diluted to a final volume of 250 ml dextrose in water 5%. This is infused once daily within 1 hour for four consecutive days. All patients allocated to the placebo group will also receive standard therapy at the discretion of their attending physicians.
- *Active drug*; patients receive 1g of clarithromycin dissolved into 20 ml water for injection and then diluted to a final volume of 250 ml dextrose in water 5%. This is infused once daily within 1 hour for four consecutive days as previously described^9, 11^. All patients allocated to the active drug group will also receive standard therapy at the discretion of their attending physicians.

***Study visits***

*Screening visit*

When a patient meets ALL inclusion criteria and NONE of the exclusion criteria, he/she can be enrolled in the study. The criteria are judged based on data available from the patient’s file. Female patients of reproductive age should be screened with a urinary pregnancy test. QT prolongation or prior arrhythmia is not considered as an exclusion criterion for the study, ^9,11^ but may be considered in the decision making of the principal investigator. The same patient cannot be enrolled twice in this study.

*Patient follow-up*

Follow-up of every patient will be done daily until day 28 or hospital discharge (whatever comes first).

Visit 1 is on day 1. Procedures of this day include:

- Recording of demographics, medical history, co-morbidities (Charlson Comorbidity Index), ^17^ SOFA score (see APPENDIX II); Acute Physiology and Chronic Health Evaluation (APACHE) II score (see APPENDIX III), available blood cell count, biochemistry, coagulation time, urine output, blood gas analysis, recording of suspected infection site, available radiological findings, relevant for the current infection microbiology and antimicrobial susceptibility testing if available, administered antimicrobials, other administered drugs and need for source infection control either by percutaneous interventions or by any operation.
- Sampling of 35 ml of venous blood; 3ml is collected into one PAXgene tube or a tube with RNA*later*®; 9ml is collected into one pyrogen-free tube; and 24ml is collected into EDTA-coated tubes
- Collection of stool culture or rectal swab
- Administration of the study drug
- Evaluation of potential adverse events

Visit 2 is on day 2. Procedures of this day include:

- Recording of SOFA score (see APPENDIX II); available blood cell count, biochemistry, coagulation times, urine output, blood gas analysis, available radiological findings, relevant for the current infection microbiology and antimicrobial susceptibility testing if available, administered antimicrobials, other administered drugs and need for source infection control either by percutaneous interventions or by any operation.
- Survival status
- Administration of the study drug
- Evaluation of potential adverse events

Visit 3 is on day 3. Procedures of this day include:

- Recording of SOFA score (see APPENDIX II); available blood cell count, biochemistry, coagulation times, urine output, blood gas analysis, available radiological findings, relevant for the current infection microbiology and antimicrobial susceptibility testing if available, administered antimicrobials, other administered drugs and need for source infection control either by percutaneous interventions or by any operation.
- Evaluation of early sepsis response, defined by at least 25% decrease of visit 1 SOFA on visit 3
- Survival status
- Administration of the study drug
- Evaluation of potential adverse events

Visit 4 is on day 4. Procedures of this day include:

- Recording of SOFA score (see APPENDIX II); available blood cell count, biochemistry, coagulation times, urine output, blood gas analysis, recording of suspected or proven infection site, available radiological findings, relevant for the current infection microbiology and antimicrobial susceptibility testing if available, administered antimicrobials, other administered drugs and need for source infection control either by percutaneous interventions or by any operation.
- Survival status
- Administration of the study drug
- Evaluation of potential adverse events

Visit 5 is on day 5. Procedures of this day include:

- Recording of SOFA score (see APPENDIX II); available blood cell count, biochemistry, coagulation times, urine output, blood gas analysis, available radiological findings, relevant microbiology and antimicrobial susceptibility testing if available, administered antimicrobials, other administered drugs and need for source infection control either by percutaneous interventions or by any operation. Given the previous data from phase IV trials, serial ECGs are not required for this protocol.
- Survival status
- Sampling of 35 ml of venous blood; 3ml is collected into one PAXgene tube or a tube with RNA*later*®; 9ml is collected into one pyrogen-free tube; and 24ml is collected into EDTA-coated tubes
- Collection of stool or rectal swab.
- Evaluation of resolution of the infection and potential recurrence of infection according to the judgment of the attending physician
- Evaluation of potential adverse events

Visit 6 is on day 6. Procedures of this day include:

- Recording of SOFA score (see APPENDIX II); available blood cell count, biochemistry, coagulation times, urine output, blood gas analysis, available radiological findings, clinically relevant microbiology and antimicrobial susceptibility testing, administered antimicrobials, other administered drugs and need for source infection control either by percutaneous interventions or by any operation.
- Survival status
- Evaluation of resolution of the infection and potential recurrence of infection according to the judgment of the attending physician
- Evaluation of potential adverse events

Visit 7 is on day 7. Procedures of this day include:

- Recording of SOFA score (see APPENDIX II); available blood cell count, biochemistry, coagulation times, urine output, blood gas analysis, available radiological findings, clinically relevant microbiology and antimicrobial susceptibility testing, administered antimicrobials, other administered drugs and need for source infection control either by percutaneous interventions or by any operation.
- Survival status
- Evaluation of sepsis response, defined by at least 25% decrease of SOFA score of visit 1
- Evaluation of resolution of the infection and potential recurrence of infection according to the judgment of the attending physician
- Evaluation of potential adverse events

Visit 8 is on day 8. Procedures of this day include:

- Recording of SOFA score (see APPENDIX II); available blood cell count, biochemistry, coagulation times, urine output, blood gas analysis, available radiological findings, clinically relevant microbiology and antimicrobial susceptibility testing, administered antimicrobials, other administered drugs and need for source infection control either by percutaneous interventions or by any operation.
- Survival status
- Evaluation of resolution of the infection and potential recurrence of infection according to the judgment of the attending physician
- Evaluation of potential adverse events

Visit 9 is on day 9. Procedures of this day include:

- Recording of SOFA score (see APPENDIX II); available blood cell count, biochemistry, coagulation times, urine output, blood gas analysis, available radiological findings, clinically relevant microbiology and antimicrobial susceptibility testing, administered antimicrobials, other administered drugs and need for source infection control either by percutaneous interventions or by any operation.
- Survival status
- Evaluation of resolution of the infection and potential recurrence of infection according to the judgment of the attending physician
- Evaluation of potential adverse events

Visit 10 is on day 10. Procedures of this day include:

- Recording of SOFA score (see APPENDIX II); available blood cell count, biochemistry, coagulation times, urine output, blood gases, available radiological findings, clinically relevant microbiology and antimicrobial susceptibility testing, administered antimicrobials, other administered drugs and need for source infection control either by percutaneous interventions or by any operation.
- Survival status
- Evaluation of resolution of the infection and potential recurrence of infection according to the attending physician
- Sampling of 33 ml of venous blood; 9ml is collected into one pyrogen-free tube; and 24ml is collected into EDTA-coated tubes
- Evaluation of potential adverse events

Visits 11-28 are on days 11-28 respectively. They include

- Recording of SOFA score if available
- Administered antimicrobials, other administered drugs and need for source infection control either by percutaneous interventions or by any operation.
- Survival status
- Evaluation of resolution of the infection and potential infection recurrence according to the judgment of the attending physician
- Evaluation of potential adverse events

If the patient is discharged before day 28, a phone call will be performed on day 28 to assess survival status, need for new hospitalization or antibiotic therapy and potential adverse events. End-of-life decisions, if any, will be recorded.

Last visit: A phone call follow-up will be done on day 90 to assess survival status. If available, data concerning any new hospitalization, or antibiotic cure and potential adverse events will be collected during that phone call. Moreover, a self or proxy-assessment of health-related quality of life will be performed through the EQ-5D-3L^™^ questionnaire on the same visit (see APPENDIX IV) ^18^.

All information will be recorded on a specific paper Case Report Form (CRF).

The procedure to follow at each study visit is shown in APPENDIX V.

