***Cost-Effectiveness analysis***

The EuroCoL EQ-5D-3L^™^ questionnaire at 90 days (proxy and telephone version) data will be used to convert patient responses into Quality-Adjusted Life-Years (QALYs), to define patient-level perception of health-related quality of life on a 0,1 scale. Deceased patients will be counted as a 0 on that scale. Quality of life will be compared with the cost of hospitalization.

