**TOTAL APACHE II SCORE: ΑPS + AGE + CHRONIC DISEASE SCORE**

**APPENDIX IV** EQ-5D-3L (UK English version)

By placing a tick in one box in each group below, please indicate which statements best describe your own health state today.

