**Anxiety/Depression**

I am not anxious or depressed ❑

I am moderately anxious or depressed ❑

I am extremely anxious or depressed ❑

To help people say how good or bad a health state is, we have drawn a scale (rather like a thermometer) on which the best state you can imagine is marked **100** and the worst state you can imagine is marked **0**.

We would like you to indicate on this scale how good or bad your own health is today, in your opinion. Please do this by drawing a line from the box below to whichever point on the scale indicates how good or bad your health state is today.

Best imaginable health state

9 0

8 0

7 0

6 0

5 0

4 0

3 0

2 0

1 0

100

0

Your own health state today

Worst imaginable

health state

**APPENDIX V** Procedures on each study visit (until day 28 or until hospital discharge)

|  | **Study visits** | | | | | | | | | | | | | | | | | | | | | | | | | | | | |  |
| --- | --- | --- | --- | --- | --- | --- | --- | --- | --- | --- | --- | --- | --- | --- | --- | --- | --- | --- | --- | --- | --- | --- | --- | --- | --- | --- | --- | --- | --- | --- |
|  | **1** | **2** | **3** | **4** | **5** | **6** | **7** | **8** | **9** | **10** | **11** | **12** | **13** | **14** | **15** | **16** | **17** | **18** | **19** | **20** | **21** | **22** | **23** | **24** | **25** | **26** | **27** | **28** | **Last** | |
| Study drug | x | x | x | x |  |  |  |  |  |  |  |  |  |  |  |  |  |  |  |  |  |  |  |  |  |  |  |  |  | |
| SOFA score* | x | x | x | x | x | x | x | x | x | x | x | x | x | x | x | x | x | x | x | x | x | x | x | x | x | x | x | x |  | |
| Survival |  | x | x | x | x | x | x | x | x | x | x | x | x | x | x | x | x | x | x | x | x | x | x | x | x | x | x | x | x | |
| CCI | x |  |  |  |  |  |  |  |  |  |  |  |  |  |  |  |  |  |  |  |  |  |  |  |  |  |  |  |  | |
| APACHE score | x |  |  |  |  |  |  |  |  |  |  |  |  |  |  |  |  |  |  |  |  |  |  |  |  |  |  |  |  | |
| Vital signs** | x | x | x | x | x | x | x | x | x | x | x | x | x | x | x | x | x | x | x | x | x | x | x | x | x | x | x | x |  | |
| Concomitant drugs/ procedures | x | x | x | x | x | x | x | x | x | x | x | x | x | x | x | x | x | x | x | x | x | x | x | x | x | x | x | x |  | |
| Infectious site identification | x |  |  | x |  |  |  |  |  |  |  |  |  |  |  |  |  |  |  |  |  |  |  |  |  |  |  |  |  | |

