**Missing values**

Missing values will be treated as such, and the number and percentage of patients or events entering each step of the analysis will be provided. The Little’s test will be used to assess whether missing values are missing completely at random.

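### The final protocol's visit table and attached form do not match its own text on the day-90 EQ-5D-3L, the only effectiveness measure for the cost-per-QALY endpoint

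*Supplement*

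**What the plan says.** Protocol version 2, Study visits, describes a day-90 telephone call. Besides survival, it collects readmission, antibiotic and adverse-event data if available, and "a self or proxy-assessment of health-related quality of life will be performed through the EQ-5D-3L" with a pointer to Appendix IV. For patients discharged before day 28 it adds a telephone call on day 28. The section closes with "The procedure to follow at each study visit is shown in APPENDIX V".

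The Cost-Effectiveness analysis section says that the "questionnaire at 90 days (proxy and telephone version) data will be used to convert patient responses into Quality-Adjusted Life-Years". It scores deceased patients 0. The SAP (Safety outcomes, follow-up paragraph) repeats that day-90 quality of life is taken by telephone from the patient or caregiver after discharge.

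Appendix V is headed "Procedures on each study visit (until day 28 or until hospital discharge", yet it carries a 'Last' column. Only the Survival row is ticked there. There is no EQ-5D row, no readmission or antibiotic row for that visit, and no mark for the day-28 call.

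Appendix IV is labelled the UK English version. It opens with "By placing a tick in one box in each group below", asks about the respondent's own health, and ends with a scale on which the respondent draws a line.

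The only missing-data rule in either document is in the SAP: "Missing values will be treated as such".

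**The concern.** Two operative instructions conflict. The visit text requires the EQ-5D-3L at day 90, while the table that the same text calls the procedure for each visit shows survival alone. The attached form also differs in mode and respondent from the version named for the analysis.

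The table's rows and ticks are those of version 1's Appendix III, written before the EQ-5D entered the protocol. The amendment log records only that the appendix moved. An oversight is therefore more likely than a choice.

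The day-90 EQ-5D is the sole effectiveness input to the secondary endpoint, cost per QALY gained. A missed questionnaire costs a value only in a patient not known to have died, because deaths are scored 0 without one. An analysis that drops patients with no score would keep every known death at 0 and lose only non-zero scores, so arm means would fall.

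**Working it through.** **Text against table and form**

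| Item | Protocol text and SAP | Appendix |
|---|---|---|
| EQ-5D-3L at day 90 | Required (Study visits; Cost-Effectiveness analysis; SAP Safety outcomes) | No row in Appendix V |
| Readmission and antibiotics at day 90 | Asked for, if available (Study visits) | No row; 'Last' ticked for survival only |
| Day-28 call after discharge | Required (Study visits; SAP Safety outcomes) | Survival ticked at visit 28; call not shown; heading stops at discharge |
| Form | Proxy and telephone version (Cost-Effectiveness analysis) | Self-completed sheet in Appendix IV |

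**Size: inputs**

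- Group size 55 and mortality 55% (placebo) and 30% (clarithromycin), from Power calculation. The 55 reproduces with two-sided alpha 0.10, power 0.8 and continuity correction (48 without the correction). It serves here only to size the survivor groups.
- Day-90 mortality is not given. The protocol's 55% and 30% are 28-day rates and stand in for it (assumption).
- Survivor utility u = 0.6, range 0.4 to 0.8 (assumption).
- Share m of survivors with no EQ-5D: 10% to 50%, equal by arm, then unequal (assumption).

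Expected survivors: 55 × 0.45 = 24.75 on placebo and 55 × 0.70 = 38.5 on clarithromycin. With m from 10% to 50%, the share of all patients with no score is 0.45m = 4.5% to 22.5% on placebo and 0.70m = 7% to 35% on clarithromycin.

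**Formula.** With d the arm's mortality, the complete-case mean score on the 0 to 1 scale is u(1−d)(1−m) / [d + (1−d)(1−m)]. The true mean is u(1−d).

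**Results at 55%/30%, u = 0.6**

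| Loss, placebo / clarithromycin | Placebo mean | Clarithromycin mean | Difference |
|---|---|---|---|
| 0 / 0 | 0.270 | 0.420 | 0.150 |
| 10% / 10% | 0.254 | 0.406 | 0.152 |
| 30% / 30% | 0.218 | 0.372 | 0.154 |
| 50% / 50% | 0.174 | 0.323 | 0.149 |
| 20% / 40% | 0.237 | 0.350 | 0.113 (−25%) |
| 40% / 20% | 0.198 | 0.391 | 0.193 (+29%) |

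Worked line, 20% / 40%:

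- Placebo: 0.6 × 0.36 / (0.55 + 0.36) = 0.216 / 0.91 = 0.237.
- Clarithromycin: 0.6 × 0.42 / (0.30 + 0.42) = 0.252 / 0.72 = 0.350.

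Every mean is proportional to u, so the percentage changes are the same at u = 0.4 and 0.8. Under equal loss up to 50%, the difference stays within about 0.005 of its true value over that range.

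**Sensitivity to mortality.** At an assumed 60%/40% with u = 0.6, the true difference is 0.120. Equal loss gives 0.118 at 25%, 0.107 at 50% (−11%) and 0.078 at 75% (−35%).

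Loss related to the survivor's health state was not computed.

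**The case against.** The strongest reply is that the EQ-5D is scheduled. Study visits requires it shortly before the sentence that points to Appendix V, and the Cost-Effectiveness section and the SAP confirm it. The table's heading limits it to day 28 or discharge. Sites record on a case report form that is not shown, and the sponsor reviews protocol and forms with investigators before enrolment. This stands: loss is a risk, and a reader who infers that no survivor will have an EQ-5D must suppose that every site ignores the text. The heading does not fully excuse the table, because the table includes and uses a 'Last' column.

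A reader might also infer that the Appendix IV form is unusable by telephone or proxy. The documents do not support that. The five items can be read aloud. The tick-box wording and drawn scale are what suit a call poorly, and nothing says that the scale feeds the QALY. Nor does any section say that Greek or Belgian sites will use the English sheet.

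Third, the SAP's General principles report the whole cost-effectiveness analysis separately, so its missing-value rule may not govern QALYs. Neither document says that survivors without a score will be dropped. This also stands. The estimator in the working is one possible analysis, and the gap is that no rule is clearly stated for this endpoint.

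Finally, the SAP anticipates 10% loss to follow-up, so patients of unknown vital status, including unrecorded deaths, would also lack a value. Hence the wording used here: patients not known to have died.

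**Conclusion.** The inconsistency is real and can be checked line by line. Appendix V omits the day-90 EQ-5D and readmission data that the text requires, and Appendix IV attaches a different form from the one the analysis names. The consequence is a possible, not a planned, loss or mis-administration of the only effectiveness measure for a secondary endpoint.

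If patients with no score are dropped, both arm means fall: at 30% equal loss, from 0.270 to 0.218 and from 0.420 to 0.372. Cost per QALY gained depends on the difference, and that barely moves under equal loss at the protocol's 55%/30% rates. It shifts materially if loss differs by arm (about a quarter either way at 20% against 40%), or if mortality is higher and loss heavy. A reader might take the fall in arm means as the bias in the endpoint, and the calculation does not support that.

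The figures rest on 28-day rates standing in for day 90, an assumed utility, assumed loss rates and a complete-case analysis that the documents do not prescribe.

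**What to change.** - **Appendix V:** add an EQ-5D-3L row and a readmission and antibiotic row ticked at 'Last', show the day-28 call for discharged patients, and correct the heading so that it covers day 90.
- **Appendix IV:** attach the telephone and proxy versions of the EQ-5D-3L, in the languages the sites use.
- **Economic analysis plan:** state that missing EQ-5D in a known survivor is imputed from survivors, for example by multiple imputation by arm, instead of dropping the patient while deaths stay at 0.

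The calls are already planned, so no visit is added. The cost is a document amendment and slightly more analysis work. Imputation by arm is one reasonable option. What matters is that the rule is fixed in advance and treats survivors without a score separately from deaths.
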